#### Dropout

If participants choose to stop the intervention, a detailed interview of the participant will be conducted to rule out the reason for the dropout. But no force will be exerted on them to continue the intervention. Common reasons for dropping out of the study will be enlisted and measures will be taken to manage them if feasible within the limits of the researcher.

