## Methods

### Study Design

A 3-arm superiority randomized controlled trial will be performed. The study flow is depicted in Figure 1. Patients with gadget addiction will be selected from the Kaumarbhritya Outpatient Department of MGACHRC Salod, Wardha as per inclusion criteria mentioned in Textbox 2. During the first visit, Parents will be asked whether they would like to deaddict their child from gadget addiction if they are willing then written informed assent will be obtained from the participants’ guardian. Participants will then complete questionnaires on the internet addiction test scale and digital addiction scale. Furthermore, participants’ social behavior and Prakruti (physical and mental constitution) will be assessed. As well as age, gender, socioeconomic status, and type of gadget he or she is using frequently, and the purpose of gadget use will be assessed. After this period, participants will be randomly allocated to both intervention groups in a 1:1 allocation ratio. After this, Medhya Rasayana will be prescribed to participants in group I according to age-wise doses at a frequency of twice a day for a period of 90 days as mentioned in Table 1. Participants allocated to group II will be counseled regarding the adverse effects of gadget addiction on physical and mental health and advised to follow the following routine daily for a period of 90 days, details of nonpharmacological interventions are described in Tables 1 and 2. Yoga (sun salutations, meditation), Targeted reduction in Gadget use time Padanshik krama, that is, reduce gadget use time by one-fourth part each week. Reduced time will be used for adventure, bravery, cognitive skill-oriented things, sports, and yoga. Patients will be counseled to play indoor and outdoor games daily. Encouragement toward attending social programs whenever required and feasible, encouragement of parent-child relationship by advising parents to spend a minimum of 2 hours of quality time daily with children and to give a reward for not using mobile with encouraging children to learn new things, participate in group activities with peers and teach etiquette. Initial training in sun salutation and the method of meditation will be given to participants and their parents at the time of enrollment. Children will be asked to do the proposed sun salutation and meditation on the assessment day. Participants not responding or not following instructions will be eliminated from the study. Group III will be the external group due to the fact that cognitive behavioral therapy requires trained professionals and there are time and financial constraints as well. Hence, in this published data of previously conducted clinical trials, cognitive behavioral therapy intervention in the management of gadgets or internet addiction will be used for comparison with Medhya Rasayana and Ayurveda nonpharmacological interventions. On the 30th, 60th, and 90th days of treatment, participants will be evaluated using the internet addiction test scale and the *DSM-5* (*Diagnostic and Statistical Manual of Mental Disorders, Fifth Edition*) scale for social behavior. A follow-up will be conducted on the 180th day to determine whether the intervention’s possible effects are lasting.

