### Assessment of Participants

All participants will be assessed for level of addiction, social behavior, and Prakruti (physical and mental constitution) before initiating the intervention during the study at 0, 30, 60, and 90 days, and on the follow-up day at180 days at Mahatma Gandhi Ayurved Hospital Salod (H). For the assessment of gadget addiction, an internet addiction test scale [31] questionnaire and a digital addiction scale [32] will be used. There are 20 statements on this questionnaire. After carefully reading each statement, participants have to choose the response (0, 1, 2, 3, 4, or 5) that best describes him or her using the 5-point Likert scale. Select the option that most accurately reflects how participants have been spending their time over the past month if 2 options seem to fit equally well. Along with participants, their parents or caretakers will be asked the following question regarding the gadget-addicted behavior of their children and the mean of both scores will be calculated to avoid bias in the study. The social behavior of the patient will be assessed by *DSM-5* [33] criteria on the proposed day Prakruti examination will conducted on the day of initiation of intervention by Ayusoft software [34].

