#### Informed Consent

Before the study begins, all participants must give written informed consent (ie, during the first visit to the hospital). Every participant will get information regarding the study’s design, objectives, data confidentiality, and the freedom to withdraw from the study at any moment without giving a reason. The original informed consent or approval from the institutional review board explicitly permits secondary analyses of the research data without necessitating additional consent.

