#### Adverse Effects

Adverse consequences are characterized as unfavorable results resulting from study involvement. This study’s potential side effects may include injury while doing yoga or Gastrointestinal system disturbances due to Medhya Rasayana avaleha. Adverse effects that occur will be noted and assessed for both the intervention and control groups.

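### The Dropout section treats a child who stops the intervention as having left the study, so outcome and adverse-effect observation after stopping is not assured

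*Protocol article*

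**What the plan says.** The Dropout section (Methods) sets the rule for a child who stops by choice: "If participants choose to stop the intervention, a detailed interview of the participant will be conducted to rule out the reason for the dropout". It adds that the child will not be pressed to continue, and then: "Common reasons for dropping out of the study will be enlisted and measures will be taken to manage them if feasible". Nothing there says whether such a child keeps the later visits.

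Five other places bear on this:

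- **Adverse Effects** names the expected harms, "injury while doing yoga or Gastrointestinal system disturbances due to Medhya Rasayana avaleha", and promises that "Adverse effects that occur will be noted and assessed for both the intervention and control groups". It gives no period and does not mention children who have stopped.
- **Assessment of Participants** states that "All participants will be assessed for level of addiction, social behavior, and Prakruti" at days 0, 30, 60, 90 and 180. Safety is not among the items listed.
- **Study Design** gives the purpose of the last visit: "A follow-up will be conducted on the 180th day to determine whether the intervention’s possible effects are lasting". It also states: "Participants not responding or not following instructions will be eliminated from the study".
- **Participants** raises the sample size from 72 to 80 per group for 10% dropout.
- **Informed Consent** promises "the freedom to withdraw from the study at any moment without giving a reason".

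**The concern.** Stopping treatment and leaving a study are different events. A child can stop taking the preparation or doing the yoga and still attend the remaining visits. If the plan treats the first as the second, later outcome and safety information on that child may never be collected.

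The loss is unlikely to fall at random. Both anticipated harms are plausible reasons for a family to stop, so observation is least assured in the children whose adverse effect was troublesome enough to end treatment. For efficacy, the comparison at days 90 and 180 would lean towards children who tolerated and accepted their allocated intervention. For harms, the later course of an event still open at stopping might not be recorded.

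**Working it through.** **1. The plan's own dropout figure.** Inputs from the Participants section: P1 = 0.622, P2 = 0.362, z-values 1.64 and 0.84, difference 0.20, dropout 10%.

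- Variance term: 0.622 × 0.378 + 0.362 × 0.638 = 0.2351 + 0.2310 = 0.4661
- n = (1.64 + 0.84)² × 0.4661 / 0.20² = 6.1504 × 0.4661 / 0.04 = 71.7, rounded up to 72
- Inflated: 72 / (1 − 0.10) = 80

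Both stated figures reproduce and are not in dispute here. What matters is what the inflation implies: dividing by 0.90 counts each dropout as contributing no outcome data, so that 80 − 8 = 72 remain. That fits a plan in which a child who stops is lost to assessment.

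**2. How many children.** 10% of 80 is 8 per group, or 16 over the two randomized groups. The article gives no share of dropouts due to an adverse effect. If that share lay between 10% and 50% (an assumption, for scale only), 16 × 0.10 = 1.6 to 16 × 0.50 = 8 children would be affected, that is about 2 to 8.

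**3. The sections side by side.**

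| Question | What the article says | Where |
|---|---|---|
| What is a child who stops called? | First a dropout, then someone leaving the study | Dropout |
| What contact is specified? | An interview about the reason | Dropout |
| What else may be done? | Common reasons listed, and managed where feasible | Dropout |
| What happens to a child who departs from instructions? | Removed from the study | Study Design |
| Who attends through day 180? | All participants, with no statement about those who stopped | Assessment of Participants |
| Is safety an item at those visits? | Not listed | Assessment of Participants |
| Are adverse effects recorded? | Yes, without period and without exception | Adverse Effects |

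The first four rows describe a plan in which departing from the intervention means leaving, or being removed. The fifth could be read to include children who stop, but only if a child classed as having dropped out still counts as a participant, which the article does not say. The last row covers events known up to and at stopping; it does not say how later information would reach the study team. The sections therefore do not settle whether a child who stops is still observed.

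**4. Dropout against Informed Consent.** One section says that an interview about the reason will take place; the other lets a family leave without giving one. These are compatible if the interview is voluntary, but the article does not say that it is.

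**The case against.** The strongest reply is that this is a condensed journal article. Following an adverse event to its resolution is detail that an article may leave to a full protocol, and its absence here is no defect. That stands, and the point does not rest on it.

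The reply can go further. A reader might infer that an exit interview is all that a stopping child receives, that follow-up ends there, and that the outcome of the event is never observed. The text does not support this. The Dropout section also plans to manage common reasons where feasible, the Adverse Effects section makes no exception for children who stopped, and no section says that they leave the visits.

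A reader might also infer that harms would be summarised only in the 72 per group who continue, so that treatment-ending events disappear from the record. Nothing limits safety reporting in that way. The interview would itself tend to bring such an event to light, and it would then be noted.

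Nor is there a strong conflict with the consent promise: being asked for a reason is compatible with declining to give one.

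What the reply does not remove is the rule as written. The article has a section on dropout, and that section equates stopping the intervention with leaving the study. This is a stated rule, not a silence, and the sample-size allowance and the removal rule agree with it.

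**Conclusion.** The point holds in limited form. The Dropout section merges two states that need separate handling, and the interview is the only contact it specifies for a child who stops. Outcome and adverse-effect observation after stopping is therefore not assured, in a group that may include children who stopped because of an anticipated harm. Events reported up to and at stopping would be noted.

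The size is about 8 children per group at the planned 10% dropout. The part of these due to harm is unknown, and no bias in an adverse-effect rate can be calculated from the article. The conclusion rests on the article's own wording and assumes that no fuller document already separates the two states. It is worth correcting because the participants are aged 6 to 16 years and the correction is small.

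**What to change.** - In the Dropout section, define two states: stopped the intervention, and withdrew from follow-up.
- Keep children who stop in the existing day 30, 60, 90 and 180 assessments unless the family withdraws from follow-up.
- Record adverse effects at those visits, and report them for all children who started their allocated intervention.
- State that the interview about the reason is voluntary, so that it agrees with Informed Consent.
- Reconcile Study Design, Assessment of Participants, Dropout and Adverse Effects, so that they agree on who remains under observation and until when.

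This changes protocol and possibly consent wording and sets no rule on treatment itself. It costs modest contact effort for about 8 children per group at the planned dropout, using visits that already exist in the schedule. The adverse-effect rate may come out less favourable than it would without this information.

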#### Informed Consent

Before the study begins, all participants must give written informed consent (ie, during the first visit to the hospital). Every participant will get information regarding the study’s design, objectives, data confidentiality, and the freedom to withdraw from the study at any moment without giving a reason. The original informed consent or approval from the institutional review board explicitly permits secondary analyses of the research data without necessitating additional consent.

#### Adverse Effects

Adverse consequences are characterized as unfavorable results resulting from study involvement. This study’s potential side effects may include injury while doing yoga or Gastrointestinal system disturbances due to Medhya Rasayana avaleha. Adverse effects that occur will be noted and assessed for both the intervention and control groups.

#### Data Storage

Every piece of information regarding the study will be stored on a central disk space on a password-protected computer. Data access will be restricted to members of the research team only.

#### Incentive

Participation in the study is completely voluntary; hence, no incentive will be provided to students.

### Ethical Considerations

The Mahatma Gandhi Ayurved College Hospital and Research Center’s (MGACHRC) Institutional Ethics Committee approved this study (registration number MGACHRC/IEC/Oct-2022/614), and it was also registered with the Clinical Trial Registry of India (registration number CTRI/2021/10/037211). We will get assent from each participant’s parents. During data analysis, measures will be taken to protect participants’ privacy. The original informed assent or approval from the institutional review board explicitly permits secondary analyses of the research data without necessitating additional assent.

## Results

In December 2023, the randomized controlled study got underway. Since participants may be in the study at any time, our goal is to complete the research by December 2024. Any significant changes to the protocol will be posted on clinicaltrials.gov. The study’s findings will be disseminated through publications.

## Discussion

### Principal Findings

Compulsive conduct is one of the symptoms of addiction that can substantially impede a person’s ability to receive therapy. Gadgets negatively affect the social life, health, and cognition of the child [35]. Hence, it is necessary to diagnose and treat gadget addiction in children as early as possible. The Medhya Rasayana avaleha was selected in this study as a pharmacological intervention. Medhya Rasayana has been popularly used as a proven therapy for the improvement of the intellect of children in India for centuries. As per Ayurveda, cognition is called Medha and it is not only related to the memory of a person but also consists of 3 components, that are Dhee (intellect), Dhruti (control of mind), and Smriti (memory). Among these 3 components, Dhruti is responsible for governing features and prevents the person from consuming destructive or nonbeneficial substances [36]. Consumption of Medhya Rasayana on a daily basis could enhance the control of the mind along with intellect and memory, which is beneficial in the management of addiction.

The nonpharmacological arm selected in this study is Satvavajaya (Ayurveda psychotherapy). It is the psycho-spiritual method and is intended for use with the mind and its associated qualities. It is mainly used as an important therapeutic to control the mind, which is heading toward unwholesome objects. Satvavajaya has multiple domains along with them, we are choosing the Vijnana (educative approach), Dhairya (supportive approach and development of coping ability), and Samadhi (psychophilosophical approach) [37]. Vijana (educative approach) and Dhairya (supportive approach and development of coping ability) are achieved in this treatment through proper counseling, which will include the adverse effects of gadget addiction on physical and mental health in a simple language that the child can understand. As well, Padanshika karma is preferred over sudden stoppage of treatment, which is part of Dhairya (supportive approach and development of coping ability). Samadhi (psychophilosophical approach) is a stage of unwavering concentration and minimizing mental fluctuations one could be distracted from unwholesome things and thoughts. This is achieved by regular meditation and yogic practices. Child externalization behavior and psychological factors like anxiety and depression are associated with gadget addiction [38,39]. The Ayurveda interventions, Medhya Rasayana and Satvavajaya have proven therapeutic effects on psychological factors [40-46]. As well as the impaired cognition in gadget addiction [47], both pharmacological and nonpharmacological interventions are beneficial in improving cognition [48].

Gadget addiction in children is one of the serious issues of concern in today’s era so, there is a need to deaddict children to maintain proper growth and development of the child. Gadget addiction in children is associated with many behavioral diseases and no cost-effective convenient therapy is available for it this study can fill the gap.

While conducting the study, the investigator may face difficulties at the level of overdiagnosis of gadget addiction in children due to overconscious parents. Another difficulty we may face in the Ayurveda nonpharmacological intervention group is the failure to follow lifestyle modifications and yogic practices. This is the first study in the Ayurveda domain using pharmacological and nonpharmacological interventions for gadget addiction. Hence the small sample size and lack of a proven Ayurvedic control group are the main limitations of this study.

### Conclusion

This research will provide crucial new information about the relative effectiveness of Ayurveda nonpharmacological therapies and Medhya Rasayana in treating children’s gadget addiction. The results will guide evidence-based treatments aimed at reducing the negative impact of excessive gadget use on this susceptible population’s psychosocial development. In the end, the findings are meant to help policy makers and medical professionals create sensible plans to deal with the rising issue of childhood gadget addiction.

## Abbreviations

C-DAC: Centre for Development of Advanced Computing
*DSM-5*: *Diagnostic and Statistical Manual of Mental Disorders* (Fifth Edition)
MGACHRC: Mahatma Gandhi Ayurved College Hospital and Research Center
